### 1.7. Hypotheses

#### 1.7.1. Primary Hypothesis

Participants in the active VeNS group will have a statistically significant reduction in their (Insomnia Severity Index) (ISI) score after four weeks of treatment (T2), compared to the control participants. The effect will be maintained at 1-month (T3) and 3-months (T4) follow-up.

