### 2.5. Sample Size 

A recent pilot study [35] used electrical vestibular nerve stimulation on 20 adult participants with mild to moderate insomnia who were given fourteen 30-min electrical vestibular stimulation for two weeks. These sessions were delivered approximately 1 h prior to sleep onset. Results showed that participants’ ISI scores had a significant reduction after the VeNS (from mean ISI at baseline: 15.7 to mean ISI at 8.15, *p* < 0.00001).

Considering this trial is a sham-controlled trial, we hypothesize a large effect in the MS group. We used G*power version 3.1.9.7 (https://stats.oarc.ucla.edu/other/gpower/, accessed on 1 April 2022) to calculate the target sample size. With a statistical power of 95% and a statistical significance level at 0.05 to detect a large between-group effect size (Cohen’s *d*) of 0.8, each group will require 25 subjects. With an estimated attrition rate of 20% at 12-week posttreatment follow-up, we require 30 subjects per group, and hence, a total sample of 60 is required in this trial.

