## 3. Statistical Analyses

All statistical analyses will be performed by R for Windows (R version 4.1.0). Normal distribution of the data will be assessed by a Q-Q plot. Descriptive analysis that include means and standard deviations (SD) for the continuous variables will be presented, while numbers and percentages for the categorical variables will also be shown. A *p* value < 0.05 is considered statistically significant. Sociodemographic differences between the active VeNS group and the sham VeNS group will be analyzed using Chi-square test and *t* test. Should there be significant differences in sociodemographic factors between the two groups, covariates will be considered as confounding variables in the statistical analyses. Normality of the primary outcome (ISI) scores will be tested by the Shapiro–Wilk test. The independent samples *t* test will be used to test the baseline difference between the two groups.

A mixed model will be used to test the group (between-subject factor), time (within-subject factor), and group × time interaction effects of the ISI score between the active VeNS group and the sham VeNS group. Post hoc comparisons between groups and time points will be conducted using a *t* test with Bonferroni correction. A Cohen’s *d* effect size for each outcome will be calculated, where *d* = 0.2, 0.5, and 0.8 correspond to small, medium, and large effect size. Participants’ total usage time will also be used to investigate the effectiveness of the VeNS on anxiety and total usage time will be used as a continuous covariate in a linear regression model for ISI total score. Missing data will be managed by multiple imputation [45] by adopting the last observation carried forward (LOCF) method.

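### No test is named as deciding the trial: the ISI contrast at T2, which leads the primary hypothesis, is left to Bonferroni post hoc t tests over a family of unstated size that the sample size did not allow for

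*Protocol article*

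**What the plan says.** Three sections of the protocol article bear on this.

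- **1.7.1 Primary Hypothesis** predicts a significant reduction in the ("ISI) score after four weeks of treatment (T2), compared to the control participants"), and then adds: "The effect will be maintained at 1-month (T3) and 3-months (T4) follow-up".
- **2.5 Sample Size** uses a single two-group effect, expressed as Cohen's d. The target is 95% power at alpha 0.05, and the result is given as "of 0.8, each group will require 25 subjects". No visit is attached to this effect. The attrition allowance refers to the last follow-up: "With an estimated attrition rate of 20% at 12-week posttreatment follow-up, we require 30 subjects per group". Multiple testing is not mentioned.
- **3. Statistical Analyses** sets p < 0.05 as the significance level. For ISI it states: "A mixed model will be used to test the group (between-subject factor), time (within-subject factor), and group"; the third effect is their interaction. The visit-level contrasts come afterwards: "Post hoc comparisons between groups and time points will be conducted using a"; the method is a Bonferroni-corrected t test. It does not say which of the three effects is primary, how many comparisons the correction covers, or whether the post hoc step depends on a significant interaction.

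**The concern.** The hypothesis asks whether active beats sham on ISI at T2, and then whether that difference lasts. None of the three model effects answers this directly.

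- The **group effect** averages over all four visits, including baseline, where randomisation leaves no expected difference.
- The **group × time interaction** has 3 degrees of freedom. A significant result gives neither the direction of the difference nor the visit at which it arises.
- The **time effect** does not compare the arms.

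The contrast that does answer the question is labelled post hoc and carries a correction of unknown size. Two things are at stake. First, the results could disagree (for example a significant interaction with a non-significant corrected T2 contrast, or the reverse), and nothing in the text says which one counts. Second, the sample size assumes an uncorrected 0.05, so its power does not carry over to a corrected T2 test.

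**Working it through.** **Inputs.** From section 2.5: d = 0.8, alpha 0.05, 25 per group before attrition and 30 after. From section 2.1: 1:1 allocation and four visits. Assumed because the article does not give them: two-sided testing, the number of comparisons k, the correlation ρ between visits, and the pattern of effect over visits.

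**Step 1: the plan's own figure.** For a two-sample t test, the noncentrality is d × √(n/2) on 2n − 2 degrees of freedom. With n = 25 this is 0.8 × √12.5 = 2.83 on 48 df. Against a two-sided critical value of 2.01, power is 79%. The stated 95% would need 42 per group two-sided, or 35 one-sided. So 25 matches about 80% power. That is a separate matter and is not counted in this point, but it means the uncorrected starting value below is 79%.

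**Step 2: the T2 contrast as one of k Bonferroni comparisons.** The same noncentrality is tested at 0.05/k. With 25 per group the critical value is 2.01 for k = 1, 2.48 for k = 3 and 3.11 for k = 16.

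| Family assumed | k | 24 per arm | 25 per arm | 30 per arm |
|---|---|---|---|---|
| T2 alone, no correction | 1 | 77% | 79% | 86% |
| Between arms at T2, T3, T4 | 3 | 61% | 64% | 73% |
| Between arms at all four visits | 4 | 57% | 59% | 70% |
| Four between arms plus 2 × 6 within arms | 16 | 38% | 40% | 51% |

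The 24 is 30 × 0.8, the number left if the full 12-week attrition had already occurred. For 80% power, n per group is 26 at k = 1 and 35 at k = 3.

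**Step 3: do the omnibus tests lose power too?** Noncentral F, equal correlation ρ between visits, 25 per arm. The interaction uses the three contrasts against baseline on 3 and 144 df. The group effect uses the four-visit mean, with variance (1 + 3ρ)/4 × 2/n, on 1 and 48 df. The adjusted T2 contrast replaces d by d/√(1 − ρ²).

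| Effect at T2/T3/T4 | ρ | Interaction | Group effect | T2, unadjusted | T2, baseline-adjusted |
|---|---|---|---|---|---|
| 0.8/0.8/0.8 | 0.3 | 67% | 85% | 79% | 83% |
| 0.8/0.8/0.8 | 0.5 | 83% | 75% | 79% | 89% |
| 0.8/0.8/0.8 | 0.7 | 97% | 66% | 79% | 97% |
| 0.8/0.5/0.2 | 0.3 | 55% | 47% | 79% | 83% |
| 0.8/0.5/0.2 | 0.5 | 71% | 38% | 79% | 89% |
| 0.8/0.5/0.2 | 0.7 | 92% | 31% | 79% | 97% |

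There is no uniform ranking. With a sustained effect the interaction is weaker than an unadjusted T2 test at ρ = 0.3 and stronger at ρ = 0.5 and 0.7. The group effect exceeds even the adjusted T2 contrast at ρ = 0.3. With a waning effect the group test is weak throughout.

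**Step 4: false-positive risk.** If success could be claimed on either the group or the interaction test, each at 0.05 and treated as independent, the risk under no effect would be 1 − 0.95² = 9.75%, about 10%. The text states no such rule.

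**The case against.** A mixed model with a group × time term and Bonferroni follow-up is conventional. Because the hypothesis also predicts maintenance at T3 and T4, a repeated-measures analysis fits it. The exact contrast and family might be set in an analysis plan that is not shown. This stands in part: the model itself is suitable. But the article does more than stay silent. It chooses the tests, and it makes the comparison that answers its own hypothesis a corrected post hoc one.

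Four stronger readings are tempting, and the article does not support them.

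- *The trial was sized for T2.* Section 2.5 names no visit, and its attrition is at 12 weeks. What it does specify is one between-group effect at an uncorrected 0.05.
- *The omnibus tests lose power.* Step 3 shows that this depends on ρ and on the effect pattern, neither of which is given. Setting a baseline-adjusted T2 contrast against the interaction also credits T2 with a covariate that section 3 does not mention.
- *The correction runs over 16 comparisons.* That count is one reading of section 3. Three or four are equally open.
- *The false-positive risk is 10%.* This needs an either-test rule that appears nowhere in the article.

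**Conclusion.** The point holds as a mismatch between the hypothesis, the sample size and the analysis. Section 3 designates no deciding test, and the T2 contrast that leads the primary hypothesis sits in a Bonferroni family of unknown size.

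The power loss at that step is certain for any family larger than one. Its size is not fixed: with 25 per arm, d = 0.8 and an unadjusted two-sided t test, power goes from 79% to 64% under an assumed family of three and to 40% under an assumed 16. Loss from the omnibus tests is possible but not established, and the risk of about 10% is conditional on a rule that the text does not state. This should be corrected before the data are analysed, because otherwise the choice of deciding result stays open after the results are known.

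**What to change.** In section 3, replace the sentences on the ISI model effects and the post hoc comparisons with wording such as:

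> *The primary test is the active-minus-sham difference in ISI at T2, estimated from the mixed model with baseline ISI adjusted for, at two-sided 0.05 without Bonferroni correction. If it is significant, the same contrast is tested at T3 and then at T4, each at 0.05 (fixed sequence), which defines maintenance. Main effects, the interaction and within-arm changes are supportive.*

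The baseline adjustment needs to be written out, because part of the gain in step 3 comes from it. Section 2.5 should then name T2 as the visit to which d = 0.8 applies.

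The cost is wording only, with no change to visits, data or recruitment. The downside is that T3 and T4 cannot be claimed if T2 fails, which agrees with a hypothesis that treats them as maintenance of an effect already shown.

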#### 1.7.2. Secondary Hypotheses

Higher data usage in the active VeNS group will be associated with larger improvement in insomnia severity, PSQI score, and quality of life after the 4-week treatment.

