### 2.6. Screening and Self-Administered Questionnaire

Participants will complete a QR code online application form soliciting sociodemographic information (age, gender, educational background, marital status, monthly household income, living circumstances, employment status, psychiatric history and duration of having anxiety symptoms (in years/months), currently taking prescribed or over the counter anxiolytics (yes/no), family history of anxiety disorder (yes/no) and other psychiatric disorders, etc.) before filling in the screening tool (Insomnia Severity Index).

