### 2.11. Ethical and Data Security Considerations

Ethical approval will be obtained from the Human Subjects Ethics Sub-committee, Hong Kong Polytechnic University. This study adheres strictly to the Declaration of Helsinki ethical principles developed by the World Medical Association. All participants will be covered by trial insurance. Potential risks involved in NeVS will be clearly indicated in the Information Sheet. Voluntary participation, anonymity and confidentiality and the right to withdraw will be respected.

Participants’ data in both groups will be stored in two separate datasets with an identifier linking these data. Both sets of data will be encrypted using TrueCrypt (http://www.truecrypt.org). The data from baseline, and the four-week, one-month and three-month follow-up will be linked according to personal data. All precautions in data protection will be taken, as suggested by TrueCrypt. To prevent leakage of personal data, only the PI will have access to the personal dataset. Written consent will be obtained from all participants. An information sheet containing the purpose of this trial and the VeNS procedures and the Modius Stress leaflet will be provided to all participants. Participants will be informed of their anonymity; withdrawal or non-compliance will not result in any consequences.

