### 2.12. Outcome Evaluation (Primary and Secondary Outcomes)

The primary objective of this study is to evaluate the effects of VeNS on participants’ insomnia severity among adults in Hong Kong. Secondary objectives include examining the effects of VeNS data usage on insomnia severity, sleep quality, and quality of life.

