#### 2.12.1. Primary Outcome

##### Insomnia Severity

Insomnia severity will be assessed by the Chinese version of the Insomnia Severity Index (ISI) which consists of 7 items measuring day and night symptoms of insomnia on individuals. This ISI consists of seven items (1: perceived difficulty, 2: falling asleep; 3: time of awakening; 4: satisfaction with current sleep pattern; 5: interference with daily functioning; 6: noticeability of others of impact of lack of sleep; 7: degree of perceived distress/concern caused by the sleep problem). Subjects will rate each question on a 5-point Likert scale (0–4), with score ranges of 0–28, with 15–21 indicating moderately severe insomnia. ISI has been used in the Chinese population with good psychometric properties, with Cronbach’s alpha 0.81 and item-to-total correlations in the range of 0.34–0.67 [39].

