#### 2.12.2. Secondary Outcomes

##### Sleep Quality

The Pittsburgh Sleep Quality Index (PSQI) [40] will be used to assess sleep quality over the past month. The PSQI consists of 19 items in total. Participants type in their responses to the first 5 questions asking about their bedtime, time taken to fall asleep, wake up time, actual sleep time, and time in bed in the past month. Next, they respond to the remaining 14 questions that ask about the frequency of sleep problems, use of sleeping pills to go to sleep and daytime sleepiness on a Likert-type scale ranging from 0 to 3, with a higher value indicating more severe sleep problem. A score of ≥5 indicates poor sleep quality. Total score ranges are 0–21. If total score increases, it indicates a decrease in sleep quality. The Chinese version of the PSQI is a reliable and valid instrument to assess sleep quality among the Hong Kong Chinese population [41].

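### The usage analysis names anxiety, which the trial does not measure, and gives a model only for ISI, so it does not match the secondary hypothesis

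*Protocol article*

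**What the plan says.** Section 3 (Statistical Analyses) of the protocol article describes the usage analysis in one sentence. Its first half says that participants' "total usage time will also be used to investigate the effectiveness of the VeNS on anxiety". Its second half says that "total usage time will be used as a continuous covariate in a linear regression model for ISI total score". Section 3 gives no other usage model.

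Section 1.7.2 states the secondary hypothesis: "Higher data usage in the active VeNS group will be associated with larger improvement in insomnia severity, PSQI score, and quality of life". The time point given there is the end of the 4 weeks of treatment (T2). Section 2.12 agrees on the outcomes: "Secondary objectives include examining the effects of VeNS data usage on insomnia severity, sleep quality, and quality of life". Objective 2 in section 1.6 names the same three. The instruments in sections 2.12.1 and 2.12.2 are the ISI, the PSQI and the SF-36, all measured at baseline and at each later time point. No anxiety scale is listed.

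Anxiety appears on the data-collection side only in section 2.6, where the application form asks about duration of anxiety symptoms, anxiolytic use and family history of anxiety disorder. Section 2.11 says that "the Modius Stress leaflet will be provided to all participants", while section 1.4 calls the device Modius Sleep.

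**The concern.** A reader following section 3 would look for an anxiety outcome and find none. The reader would then fit a model for one of the three outcomes in the hypothesis, with the arm, the time point and the handling of baseline left open.

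This is the only analysis offered for the only secondary hypothesis. If it is not aligned before the data are seen, outcome, population and adjustment can all be chosen afterwards. Usage is also a behaviour that arises after randomisation, so its slope is easily read as a dose-response when it may partly reflect who chooses to use the device.

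**Working it through.** **Step 1. Set the texts side by side.**

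| Element | Secondary hypothesis (1.7.2) | Usage analysis (3) |
|---|---|---|
| Outcomes | Insomnia severity, PSQI, quality of life | Anxiety (not measured); then ISI total score |
| Quantity | Improvement | Total score; change or baseline term not stated |
| Group | Active VeNS | Participants; arm not stated |
| Time | After 4 weeks (T2) | Not stated |

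The outcome row is a direct conflict. PSQI and quality of life have no usage model. The other three rows show a mismatch or a silence.

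**Step 2. Range of the exposure.** Section 2.8 plans 20 sessions of 30 minutes: 20 × 0.5 h = 10 h, as stated there. One week is 5 × 0.5 h = 2.5 h, which is the level below which section 2.9 sends a reminder. Usage is therefore steered towards one value, and its spread may be small. The document gives no usage SD.

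**Step 3. Effect of pooling, if the arms are pooled.** With equal mean and spread of usage in two equal arms, the pooled slope is the average of the arm slopes: (b_active + b_sham)/2. With b_sham = 0 it is b_active/2.

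**Step 4. Effect of leaving out baseline, if it is left out.** The bias in the usage slope is r × β × SD(baseline)/SD(usage), where r is the usage-baseline correlation and β the slope of T2 ISI on baseline ISI. None of these is in the document. Assume SD(baseline) = 3 points, SD(usage) = 2 h, β = 1 and residual SD = 4 points:

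- r = +0.3: 0.3 × 1 × 3/2 = +0.45 points per hour
- r = 0: no bias
- r = −0.3: −0.45 points per hour

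A positive r works against the hypothesis, which expects lower ISI with more usage. A negative r would imitate it. Even at r = 0 precision is lost: the residual SD is √(4² + 3²) = 5 instead of 4, so the standard error is 25% larger.

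**Step 5. Simulation under the same assumptions** (30 per arm, 3,000 runs, two-sided 0.05; baseline and usage drawn as normal, without truncation at the ISI entry limit or at 10 h). Each cell gives the mean slope and the share of significant results.

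| Truth | Pooled, no baseline | Active only, no baseline | Active only, with baseline |
|---|---|---|---|
| No usage effect, r = 0.3 | +0.48; 29% | +0.47; 18% | +0.01; 5% |
| Active −1, sham 0, r = 0 | −0.50; 30% | −0.99; 53% | −0.99; 69% |
| Active −1, sham 0, r = 0.3 | −0.04; 5% | −0.54; 20% | −0.98; 65% |

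The slopes agree with steps 3 and 4. In the last row, for example, −0.50 + 0.45 = −0.05 for the pooled model.

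**Step 6. What an active-arm analysis can detect.** By Fisher's z, 80% power at two-sided 0.05 needs |r| = tanh(2.80/√(n − 3)). For n = 30 this is tanh(2.80/√27) = 0.492. For n = 24 it is tanh(2.80/√21) = 0.545. The 24 is 30 less the 20% attrition that section 2.5 gives for the 12-week follow-up; attrition at T2 is not given, so 24 is a cautious figure.

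**The case against.** The strongest reply is that the sentence mentioning anxiety goes on to name the ISI as the response, so the slip is plain and the ISI part can be understood. Calling usage a covariate does not exclude other terms. Section 1.7.2 already supplies the active group and the 4-week time point. An article condenses a fuller protocol, and the terms of a secondary model are often left to it or to the analysis plan.

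Most of this stands. A reader might infer that baseline ISI is omitted, that the arms are pooled, and that the secondary hypothesis therefore cannot be tested. The document does not support that: it is silent on these terms, and silence does not show what the model contains. A reader might also infer that the model would produce a false dose-response from baseline severity. Under the assumption that more severe participants use the device more, the bias runs the other way and would hide one. The document gives no correlation from which to settle direction or size.

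Two things are not answered. The article does name an outcome that the trial does not measure, and it does write a usage model for one outcome where the hypothesis names three.

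On the screening form, a reader might infer that the anxiety items are misplaced and that sleeping-pill use is not asked. The list in section 2.6 is open-ended, and questions on psychiatric history and medication may serve the exclusions in section 2.4. Neither inference is secure. Low power for usage is not an error either, since section 2.5 sizes the trial on a between-group effect.

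**Conclusion.** The point holds as a misalignment between the stated usage analysis and the secondary hypothesis. It is certain that anxiety is not an outcome and that PSQI and quality of life have no usage model in the article. It is also certain that the ISI model as written does not state the arm, the time point or improvement.

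The statistical cost is conditional. Pooling halves the slope only if the arms are pooled, the sham slope is zero and usage is distributed alike in equal arms. Omitting baseline costs precision (25% on the standard error under the assumed SDs). It biases the slope only if usage correlates with baseline severity: about ±0.45 ISI points per hour for r = ±0.3 under those assumptions.

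The primary between-group comparison is not touched. The correction should be made because it is nearly free and closes choices that would otherwise be made after the data are seen.

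**What to change.** In section 3, replace anxiety with insomnia severity, sleep quality and quality of life. For each of ISI, PSQI, SF-36 PCS and SF-36 MCS, regress the T2 score on total usage and the baseline value of that outcome. Take the active-arm usage slope as the test of the hypothesis. Either fit the active arm alone, or fit both arms with arm and usage × arm terms and report the sham slope for comparison. The sham slope isolates a device effect only if usage relates to outcome in the same way in both arms apart from that effect. Label the result an exploratory association rather than a causal dose-response, and bring the word effects in section 2.12 into line with association in sections 1.6 and 1.7.2.

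Separately, reconcile the leaflet name in section 2.11 with the device name in section 1.4. Check that the screening form asks about sleeping-pill use, on which inclusion criterion 4 in section 2.3 turns, and keep the existing psychiatric history items.

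The cost is an edit to the text and a check of one form. Baseline scores are collected, and the device logs usage under procedures common to both arms (section 2.8.2). The drawback is a few extra model terms in an analysis that already has low power for usage.

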## Abstract

Insomnia is a common health problem in the general population. There are different ways to improve sleeping habits and quality of sleep; however, there is no clinical trial using transdermal neurostimulation to treat individuals with symptoms of insomnia in Asia. This gives us the impetus to execute the first study in Asia which aims to evaluate the efficacy of Electrical Vestibular Stimulation (VeNS) on individuals with insomnia in Hong Kong. This study proposes a two-armed, double-blinded, randomized, sham-controlled trial including the active VeNS and sham VeNS group. Both groups will be measured at baseline (T1), immediately after the intervention (T2), and at the 1-month (T3) and 3-month follow-up (T4). A total of 60 community-dwelling adults aged 18 to 60 years, with insomnia symptoms will be recruited in this study. All subjects will be computer randomized into either the active VeNS group or the sham VeNS group on a 1:1 ratio. All subjects in each group will receive twenty 30-min VeNS sessions during weekdays, which will be completed in a 4-week period. Baseline measurements and post-VeNS evaluation of the psychological outcomes (i.e., insomnia severity, sleep quality and quality of life) will also be conducted on all participants. The 1-month and 3-month follow-up period will be used to assess the short-and long-term sustainability of the VeNS intervention. For statistical analysis, a mixed model will be used to analyze the repeated measures data. Missing data will be managed by multiple imputations. The level of significance will be set to *p* < 0.05. Significance of the study: The results of this study will be used to determine whether this VeNS device can be considered as a self-help technological device to reduce the severity of insomnia in the community setting. We registered this clinical trial with the Clinical trial government, identifier: NCT04452981.

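### Multiple imputation carried out by LOCF is in effect single imputation; it conflicts with the abstract and can bias the ISI comparison in a direction that depends on the dropout pattern

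*Protocol article*

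**What the plan says.** Section 3 (Statistical Analyses) states: "Missing data will be managed by multiple imputation [45] by adopting the last observation carried forward (LOCF) method". The abstract says only: "Missing data will be managed by multiple imputations". It does not mention LOCF.

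The analysis to which this applies is also in section 3: "A mixed model will be used to test the group (between-subject factor), time (within-subject factor), and group × time interaction effects" on the ISI score, followed by Bonferroni-corrected post hoc t tests.

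The primary hypothesis (section 1.7.1) has two parts. The first is a larger ISI reduction "after four weeks of treatment (T2), compared to the control participants". The second is durability: "The effect will be maintained at 1-month (T3) and 3-months (T4) follow-up".

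Section 2.5 gives the expected loss: "With an estimated attrition rate of 20% at 12-week posttreatment follow-up, we require 30 subjects per group". This is one rate, cumulative to the last visit, with no split by arm or by visit.

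**The concern.** Multiple imputation draws several plausible values for each missing cell, so that the spread between completed datasets carries the uncertainty about what was not seen. LOCF copies one earlier value. The two cannot both fill the same cell, so a reader cannot tell which will be run, and they can give different answers.

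The choice touches the primary outcome. For someone lost before T2, LOCF copies the baseline ISI, which assumes no change. That is not neutral when the pilot in section 2.5 reports a fall from 15.7 to 8.15. For someone lost after T2, LOCF sets later change to exactly zero, which assumes for that person the durability that the second part of the primary hypothesis is meant to test.

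**Working it through.** **Inputs from the protocol article.** 30 per arm, 60 in total, d = 0.8 and 20% attrition by the 12-week follow-up (section 2.5): 0.20 × 60 = 12 participants. The stated 25 per group does not reproduce at 95% power and d = 0.8 (42 per group by a two-sided t test). That is a separate matter and nothing below depends on it.

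**Step 1: the contradiction.** With M imputations, Rubin's rules give total variance T = W + (1 + 1/M) × B, where W is the within-imputation and B the between-imputation variance. Under LOCF every completed dataset is the same, so B = 0 and T = W. This is single imputation, with copied values counted as observed.

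**Step 2: loss after T2.** Let a share q be lost equally in both arms, at random within arm. D2 and D4 are the true group differences at T2 and T4.

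LOCF difference at T4 = (1 − q) × D4 + q × D2

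With q = 0.20 and D2 = 0.8 SD:
- D4 = 0: 0.8 × 0 + 0.2 × 0.8 = 0.16
- D4 = 0.4: 0.8 × 0.4 + 0.2 × 0.8 = 0.48
- D4 = 0.8: 0.8 × 0.8 + 0.2 × 0.8 = 0.80, so no bias

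LOCF hides 20% of whatever waning there is.

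**Step 3: loss before T2.** With equal loss q, the difference becomes (1 − q) × D. For q = 0.20 and D = 0.8 it is 0.64.

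**Step 4: simulation at T4.** 30 per arm, 2,000 runs, baseline-adjusted comparison, 20% lost equally. Assumptions not in the documents: sham change of −0.5 SD, correlation 0.6 between adjacent visits, dropout at random within arm.

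| Scenario | LOCF | Proper multiple imputation |
|---|---|---|
| Lost after T2, 0.8 at T2, 0 at T4 | 0.16; rejection 10.6%; coverage 89% | 0.00; 4.0%; 96% |
| Lost after T2, 0.8 at T2, 0.4 at T4 | 0.49 | 0.40 |
| Lost after T2, 0.8 maintained | 0.80; coverage 94% | 0.80; coverage 95% |
| Lost before T2, 0.8 throughout | 0.64; power 73% | 0.80; power 83% |

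**Step 5: unequal loss before T2, no true effect.** The false benefit for active equals (dropout in sham − dropout in active) × common improvement. Assumptions: both arms improve by 5 ISI points, SD 5, correlation 0.5, 30 per arm, and one uncorrected t test at T2.

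| Dropout, active / sham | False difference | Type I error |
|---|---|---|
| 20% / 20% | 0 | about 5% |
| 8% / 12% | 0.04 × 5 = 0.2 points | 5.3% |
| 5% / 15% | 0.10 × 5 = 0.5 points | 6.3% |
| 10% / 30% | 0.20 × 5 = 1.0 point | about 11% |

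If the heavier loss is in the active arm, the sign reverses.

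**The case against.** The best defence is that this is one badly worded sentence in a condensed article. The abstract points to multiple imputation, and details of the imputation model belong in a fuller plan. The second part stands: the missing number of imputations or list of covariates is not a finding. The first does not rescue the sentence, because the article names a method and the method named cannot be carried out as described.

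A reader might go further and infer that LOCF builds the maintained effect into the result. The documents do not support that. The pull toward T2 acts only on participants lost after T2, who are at most about 20% as planned. If the effect vanishes by T4, LOCF leaves one fifth of it, which is residual bias and not maintenance. If the effect truly persists and all losses follow T2, the bias is zero. Equal early loss works against the trial's hypothesis.

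A reader might also take 11% as this trial's error rate, or about 17% if the pilot's change of 15.7 − 8.15 = 7.55 points is used in both arms (false difference 0.20 × 7.55 = 1.51 points). Neither follows. Both need a threefold imbalance between arms and all 20% attrition before T2, whereas section 2.5 gives one rate cumulative to the 12-week follow-up, and section 2.8.2 puts the sham arm through identical procedures. The 7.55 points come from an uncontrolled pilot of active stimulation, and nothing in the documents supports that improvement under sham. The simulated test is also not the planned one. If Bonferroni covers three post-baseline contrasts (an assumption), the 10%/30% case gives 4.7% for the T2 contrast against a nominal 1.7%. Inflation persists in relative terms, but at a different level.

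**Conclusion.** The sentence is wrong as written and should be corrected. Its two halves are incompatible, it disagrees with the abstract, and following its LOCF half would give single imputation of the primary outcome.

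The consequence is conditional. LOCF can shrink a real effect, mask waning, or create a false difference in either direction. Which of these occurs depends on when participants leave and from which arm, and the documents settle neither. The bias formulas in steps 2, 3 and 5 are exact for dropout at random within arm. The error rates, power and coverage rest on the assumed SD, correlation, improvement and dropout split, and should be read as illustrations. With equal dropout and no true effect, type I error is not inflated.

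**What to change.** In section 3, delete the clause that brings in LOCF and name one primary method valid under missing at random. Either of these will do:

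- the planned mixed model, fitted by likelihood to all observed ISI scores of all randomised participants, with no imputation; or
- proper multiple imputation, with group, baseline ISI and the observed ISI visits in the imputation model, followed by the same mixed model and combined by Rubin's rules.

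The second agrees with the abstract as it stands. If the first is chosen, the abstract's sentence should be changed to match. A sensitivity analysis for data missing not at random is a sensible optional addition, not part of the correction.

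The cost is one sentence and a little R code, with no change to sample size, visits or conduct. It should be settled before anyone sees outcome data by arm, so that the method is not chosen with the results in view.
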